**FIGURE 1 F1:**
[figure not shown]
Course of the study for each patient.

At all three points in time ISAm is evaluated. Additionally, patients complete several questionnaires for emotional well-being. Cognitive functions are assessed using an elaborate neuropsychological test battery. Up to 30 patients will undergo a resting-state fMRI and structural MRI scan. Patients who have completed the intervention protocol can take part in an interview to report possible changes in their everyday life. For clarification, Figure 2 gives an overview of the tests performed at each measurement point. All patients, independent of their study group, complete all tests in the same order. For some neuropsychological tests parallel forms are available. For those tests, the applied version at each time point is randomly selected after a patient’s group assignment. It has to be noted, that all measurements are performed during the medication ON-state. Hereafter, primary and secondary outcomes, as well as all measurement procedures are further elaborated.

**FIGURE 2 F2:**
[figure not shown]
Comprehensive overview of all three measurement points.

### Outcome Measures

The main goal of this study is to increase self-awareness for motor symptoms. Therefore, the primary outcome for efficacy testing is a global ISAm-score. To be precise, mainly its change from baseline to post-intervention assessment is analyzed to evaluate the effectiveness of IPSUM. Changes of ISAm from baseline to follow-up are considered as a secondary outcome. However, we determined several other secondary outcomes like general neuropsychological test performance, the congruence between neuropsychological test performance and subjective daily life impairment (ISAc) and the congruence between objective neuropsychological test performance and subjective test performance (metacognition). Also, changes of several PD related symptoms (depression, apathy, impulsivity, sleeping problems) and affective states (stress, anxiety, quality of life, mindfulness) are analyzed. The aforementioned secondary outcomes comprise all changes from baseline to post measurement as well as changes from baseline to follow-up measurement. Additionally, structural neurobiological changes in the Insula and Cingulate Cortices, as well as any kind of reported subjective changes during the semi-structured interview are also considered when IPSUM’s effectiveness is evaluated.

### Motor ISA-Assessment

A common method to evaluate self-awareness is by comparing self and outside assessments. In this study we use the recently developed and validated measurement method by Maier et al. (2015). The patient is shown several video clips where a healthy person demonstrates various movements. The task for the patient is to repeat the movement him/herself as seen in the video clip. The following 15 symptoms are examined:

1.Sitting on a chair: resting tremor (left and right hand), dyskinesia.2.Right hand pronation-supination: speed and amplitude of movement, dyskinesia.3.Left hand pronation-supination: speed and amplitude of movement, dyskinesia.4.Arising from a chair: resting tremor (left and right hand), dyskinesia.5.Walking down an aisle: resting tremor (left and right hand), dyskinesia.

The symptoms are distributed across the four subscales dyskinesia, resting tremor right hand, resting tremor left hand and bradykinesia. Following each task, the patient rates his/her performance on a dichotomous scale whether the movement was impaired or not. Regarding the perception of a symptom, in total each patient answers 15 questions with either yes or no. The whole procedure is recorded by video. Later, independent raters evaluate the movements as well. In case of any discrepancies – if the patient does not see any impairment, although the raters do – an impaired self-awareness is noted. For each symptom, irrespective of the patient’s awareness, they also rate its severity according to UPDRS-III (values range 0–4; 0 = normal/absent; 1 = mild; 2 = moderate; 3 = severe; 4 = unable to perform). This procedure allows the calculation of two independent scores: one score for overall motor impairment severity and a second score for ISAm severity. While the motor impairment score is calculated by summing up all motor severity ratings, the ISAm score is calculated by summing up all motor severity ratings of the potential 15 discrepancies. Hence, both scores can vary between 0–60. In the medication ON-state the ISAm global score can also be divided into subscores for impaired self-awareness for hypokinetic symptoms (ISAm-Hypo for tremor and bradykinesia) and hyperkinetic symptoms (ISAm-LID).

### Assessment of Cognitive Performance, Cognitive-ISA and Metacognition

Each patient’s cognitive performance is evaluated at baseline measurement. To identify patients with mild cognitive impairment (MCI), MCI-Level II-Assessment is applied. To the best of our knowledge, no established neuropsychological test battery exists to perform level II testing. Therefore, we have compiled a test battery ourselves, while also taking into account the guidelines of diagnostic criteria for MCI in PD (Litvan et al., 2012). To differentiate between single- and multiple domains of PD-MCI, for research purposes it has been strongly recommended to use two different neuropsychological tests for each cognitive domain. Table 1 specifies the neuropsychological tests used for this purpose.

**TABLE 1 T1:** Overview of the applied neuropsychological test battery.

Domain	Test I	Test II
Attention/Working memory	TAP: Sustained attention	WMS-R: Digit span forward/backwards
Executive Functioning	RWT: Alternating semantic verbal fluency	Trail Making Test A + B
Language	WAIS-IV: Similarities	WAIS-IV: Vocabulary
Memory	VLMT	ECFT-MI: Recognition Trial
Visuospatial Ability	WMS-R: Spatial Span forward/backward	ECFT-MI: Matching Trial

*ECFT-MI: Extended Complex Figure Test – Motor Independent Version (Fastenau, 1996); RWT: Regensburg verbal fluency test (Aschenbrenner et al., 2001); TAP: test battery for attention (Zimmermann and Fimm, 2002); VLMT: Verbal learning and memory test (Helmstadter et al., 2001); WAIS-IV: Wechsler Adult Intelligence Scale – Fourth Edition (Wechsler, 2008); WMS-R: Wechsler Memory Scale-Revised (Härting et al., 2000).*

For time-economic reasons and to minimize patient strain, full MCI-Level II-Assessment cannot be performed during post- and follow-up measurement. To investigate the effects of mindfulness on cognitive performance regardless, one test for each domain is applied at these time points. For this purpose, tests listed in the column “Test I” are used. Each patient also completes the Montreal Cognitive Assessment [MoCA (Nasreddine et al., 2005)]. As mentioned before, some neuropsychological tests offer parallel versions. To minimize training effects caused by performing the same test more than once, the applied test version of the Regensburg verbal fluency test, the Verbal learning and memory test and the MoCA is chosen randomly for each patient. It is possible that the same test version is assigned to a patient more than once. In addition, neuropsychological data is used to evaluate two kinds of cognitive awareness. For one, self-awareness for performance level in daily life and secondly, metacognition for cognitive performance in neuropsychological tests.

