**Methods:**

The effectiveness of IPSUM is evaluated by comparison of an intervention group with a waitlist-control group. A pre-post design with an additional 8-week follow-up measurement is applied, resulting in three measurement points: before, directly after and 8 weeks after completing the intervention protocol. In total, up to 180 non-depressed PD patients without severe cognitive impairment (non-demented) will be included. The primary outcome is a quantitative score for measuring ISAm. Secondary outcome measures are affective changes, neuropsychological performance and self-awareness of cognition. At pre- and post-measurement an fMRI scan is performed to connect behavioral and neurobiological findings. At post- and follow-up-measurement each patient will take part in a semi-structured interview to explore IPSUM’s impact on self-awareness and patients’ everyday lives.

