### Planned Statistical Analyses

The results of a power analysis suggest, that a total of up to 166 patients (83 patients per group) might be needed to detect a significant effect. By applying a group sequential study design the number of patients needed is raised to 180 to allow for interim analyses to be performed after including 60 and 120 patients, respectively. To the best of our knowledge the motor ISA-Assessment has not been applied in a longitudinal study design. Depending on the results of these interim analyses or due to economic reasons, the study might be stopped beforehand.

Demographic and baseline characteristics will be compared using *t* tests or other non-parametric methods, if necessary. To analyze most of the primary and secondary outcomes, performing repeated-measures mixed model analyses of covariance will be essential. Independent variables will be group (intervention and waitlist) and time (pre, post and 8-week follow-up) and also their interaction. Baseline measure, the amount of medication (levodopa equivalent daily dose) and depression scores will be included as covariates. To specifically analyze ISAm scores, which are the main outcome, and to determine their degree of objectiveness, inter-rater reliability will be computed for each measurement point in time.

In order to get more insight into possible mechanisms of mindfulness, ISA and their connection to each other, several moderation and mediation analyses are planned. For example, we expect the number of completed training sessions, motor symptom severity and patients’ general cognitive performance level to be possible moderating factors affecting mindfulness scores itself and/or the relationship between mindfulness and ISA. Among others, mediating factors considered will be cognitive performance of sustained attention and questionnaire scores of negative emotions like anxiety and depression. Of course, neurobiological changes will be included as well.

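### Parallel test versions may recur within a patient, which weakens the aim of limiting training effects and adds avoidable noise to three secondary cognitive tests

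*Protocol article*

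**What the plan says.** Under Assessment of Cognitive Performance, Cognitive-ISA and Metacognition, the protocol article gives the purpose of the parallel versions: "To minimize training effects caused by performing the same test more than once". For the Regensburg verbal fluency test (RWT) and two further tests, the version is drawn by chance: "the Verbal learning and memory test and the MoCA is chosen randomly for each patient". The next sentence concedes: "It is possible that the same test version is assigned to a patient more than once". Study Design (text after Figure 1) places the draw at visit level: "the applied version at each time point is randomly selected after a patient’s group assignment".

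There are three visits, "resulting in three measurement points: before, directly after and 8 weeks after completing the intervention protocol". After baseline the battery shrinks to one test per domain: "tests listed in the column “Test I” are used". In Table 1 that column holds the RWT for executive functioning and the VLMT for memory, so each is the only repeated test of its domain.

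Outcome Measures lists neuropsychological performance, ISAc and metacognition as secondary outcomes, analysed as change from baseline to post and to follow-up. The objective side of executive ISAc is verbal fluency alone. The covariates named in Planned Statistical Analyses are the baseline measure, levodopa equivalent dose and depression score. Test version is not among them, and the number of versions per test is not stated.

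**The concern.** Parallel versions protect against practice only when a patient meets a new one. A draw that lets versions recur gives some patients a version-specific gain at post or follow-up (remembered words, a rehearsed category) and spares others, by chance. That difference between patients has nothing to do with IPSUM, yet it enters the change scores of the RWT, VLMT and MoCA. It also enters the ISAc and metacognition scores that use them. Executive ISAc is the most exposed because no second test dilutes the error.

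This is a stated rule that works against its own stated purpose, not a detail left to a fuller document. What is at stake is the precision of secondary outcomes.

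**Working it through.** The article gives no repeat rate, number of versions or practice gain, so there is no figure to reproduce.

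**Inputs from the article.** Three visits; a random version at each visit; repeats allowed; up to 180 patients ("the number of patients needed is raised to 180 to allow for interim analyses").

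**Assumed inputs.** k equally likely versions, drawn independently at each visit; g, the extra gain from meeting the same version again, in SD units; r, the test-retest correlation.

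**Step 1: how often versions recur, per test.** P(post = baseline) = 1/k. P(at least one repeat in three visits) = 1 − (k−1)(k−2)/k².

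| k | Post = baseline | Of 180 | Any repeat, three visits |
|---|---|---|---|
| 2 | 50% | 90 | 100% |
| 3 | 33.3% | 60 | 77.8% |
| 4 | 25% | 45 | 62.5% |
| 6 | 16.7% | 30 | 44.4% |

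Without replacement, the baseline-post rate is 0% for any k ≥ 2, and the three-visit rate is 0% for k ≥ 3. With k = 2 some repeat over three visits is unavoidable under any scheme, so the 100% in that row is no argument against this one.

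**Step 2: added noise.** With q = 1/k, a gain g that applies to a random share q of patients adds g²q(1−q) to the variance of the baseline-post change. Without it, that variance is 2(1−r) = 0.6 at r = 0.7. Let f be the ratio of the new SD to the old. A comparison with 80% power (an assumed benchmark) then has power Φ((1.960 + 0.842)/f − 1.960). For k = 3, q(1−q) = 0.2222:

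| g | Added variance | Relative to 0.6 | SD rise | Power |
|---|---|---|---|---|
| 0.3 | 0.0200 | 3.3% | 1.7% | 78.7% |
| 0.5 | 0.0556 | 9.3% | 4.5% | 76.4% |
| 0.8 | 0.1422 | 23.7% | 11.2% | 71.2% |

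Over k = 2 to 4, r = 0.5 to 0.8 and g = 0.2 to 0.8, the SD rises by 0.4% to 18%. The planned model adjusts for baseline. On that scale the residual variance is 1 − r² = 0.51, and the middle row becomes 0.0556/0.51 = 10.9%, so the picture is the same.

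**Step 3: chance imbalance.** With 90 per arm and k = 3, the SD of the between-arm difference in repeat share is √(2 × 0.2222/90) = 0.070. At g = 0.5 this is 0.035 SD in the mean change. It is the Step 2 variance seen at arm level, not a second effect.

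**Step 4: the price of always changing version.** If versions differ in difficulty with variance s², independent draws put 2s² into the change score. Draws without replacement put in 2s²k/(k−1), which is larger by a factor of 2, 1.5 or 1.33 for k = 2, 3 or 4. Without a version term, changing version therefore pays only if g²(k−1)/k² exceeds 2s²/(k−1), that is, if s < g(k−1)/(k√2). At k = 3 and g = 0.5 this means s < 0.24 SD. A version term in the model removes the average differences in difficulty.

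**The case against.** The strongest case for the plan has four parts.

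- **The aim is partly met.** One fixed version would mean 100% repeats at post; a random draw cuts that to 1/k. This stands. A reader might infer that the rule defeats its purpose, but the figures do not support that.
- **Nothing is biased.** Versions are drawn at random under one rule for both arms, so the average practice gain is equal in expectation and drops out of the group-by-time comparison. This stands. A reader might infer bias, or that every baseline-to-post comparison suffers. The article supports neither: ISAm, the questionnaires, imaging and the other Test I measures are untouched. General ISAc sums over all tests, which dilutes the effect. A practice gain may also lift the patient's self-rating, which would soften the effect on metacognition.
- **The mechanism is partly inferred.** The article does not use the terms independent or with replacement. With two versions and three visits, any scheme must repeat one, so the sentence allowing repeats does not prove replacement. Read with the statement that "For those tests, the applied version at each time point is randomly selected", an independent draw is the natural reading, but the rates rest on it and on the unstated k. Balancing within arm is neither stated nor excluded.
- **Changing version has a price.** Differences in difficulty then weigh more in the change score (Step 4). This stands, and it is why the fix needs a version term.

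None of this shows a benefit from letting versions recur once version is in the model.

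**Conclusion.** The point holds in a limited form. The rule weakens its stated aim and costs precision in three tests and the secondary scores built on them. The loss is small to moderate: at k = 3 and r = 0.7, the change-score SD rises by about 2% to 11% for a gain of 0.3 to 0.8 SD, and 80% power falls to about 79% to 71%. The values of k, g and r, and equal independent draws, are assumptions. The net gain from changing version also depends on how far the versions differ in difficulty, which the article does not give. There is no expected bias between arms and no effect on the primary outcome. The change is worth making because it is cheap, not because the trial's main conclusion depends on it.

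**What to change.** - State the number of versions per test.
- Give each patient a random order of versions without replacement, counterbalanced within arm. Where only two versions exist, use different ones at baseline and post, and set one rule for all patients on which of the two is reused at follow-up.
- Record the version at every visit and include it as a term in the models for the cognitive outcomes. For patients already enrolled, add a term for whether the version had been seen before. The draw is random in both arms, so adjusting for it is safe.

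The cost is an allocation list in place of a random draw, plus one or two model terms, with no added testing. There are two downsides. Differences in difficulty weigh more when versions always change, which the version term addresses. Recruitment is ongoing (Abstract, Results), so a change now mixes two allocation procedures. The date of the change should be reported.

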#### Impaired Self-Awareness of Cognition

To investigate impaired self-awareness of cognition (ISAc), subjective cognitive impairment in everyday life is compared with the more objective performance in neuropsychological tests. Subjective cognitive impairment in general is assessed by using the Cognitive Failures Questionnaire [CFQ (Broadbent et al., 1982)]. Additionally, for impairment of executive functions the Dysexecutive Questionnaire [DEX (Wilson et al., 1998)] is applied. Higher scores reflect higher subjective impairment in both questionnaires. For further statistical analysis, questionnaire and neuropsychological test raw data is transformed into standardized z-scores to allow better comparison. A delta score is calculated by subtracting subjective scores from objective scores. Beforehand, depending on the analytical objective, the transformed values of all neuropsychological tests are either summed up for reflecting general cognitive performance, or only verbal fluency performance is taken into account to reflect executive cognitive performance. Impaired self-awareness of cognition occurs if objective neuropsychological test performance appears to be worse than subjective impairment in everyday life. This is reflected by a positive delta score. A similar method has been used before to study anosognosia of memory deficits in Alzheimer’s Disease (Vannini et al., 2017).

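### The ISAc delta score, as written, contradicts its own sign rule, and its general version sets a sum of test z-scores against a single questionnaire z-score

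*Protocol article*

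**What the plan says.** The rule is in the protocol article, section Impaired Self-Awareness of Cognition. Subjective impairment is measured by the CFQ (general) and the DEX (executive), and "Higher scores reflect higher subjective impairment in both questionnaires". Then "questionnaire and neuropsychological test raw data is transformed into standardized z-scores to allow better comparison". For the objective side, the transformed values of all tests "are either summed up for reflecting general cognitive performance", or "only verbal fluency performance is taken into account to reflect executive cognitive performance". The score itself: "A delta score is calculated by subtracting subjective scores from objective scores". The construct: "Impaired self-awareness of cognition occurs if objective neuropsychological test performance appears to be worse than subjective impairment in everyday life". The sign rule: "This is reflected by a positive delta score".

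The parent section (Assessment of Cognitive Performance, Cognitive-ISA and Metacognition) lists ten tests in Table 1, two per domain, for the baseline battery. For the post and follow-up visits it says that "one test for each domain is applied at these time points", namely the Test I column. Outcome Measures lists ISAc among the secondary outcomes, as change from baseline to post and from baseline to follow-up.

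**The concern.** A discrepancy score works only if both sides run in the same direction and on the same scale. Here the subjective side is explicitly an impairment score, while the objective side is described as performance. Subtracting one from the other gives something close to overall cognitive health (good tests, few complaints), not the gap between what the tests show and what the patient reports. The stated sign rule then points the wrong way for the patients of interest.

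Scale is a second problem. If several z-scores are added and one questionnaire z-score is subtracted, the difference is driven by the tests, and the self-report side hardly counts.

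At stake is whether the trial can say anything about cognitive self-awareness. The Introduction expects an effect on it, the Conclusion names it, and Planned Statistical Analyses uses it for neural correlates. Strengths of This Study acknowledges that the ISAc analyses are not validated, so the written definition is all that an analyst has to go on.

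**Working it through.** The plan gives no figure to reproduce, so the check applies the stated rule.

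**Inputs.** O = objective z, higher = better (inferred from the word performance; no coding rule is given). S = CFQ or DEX z, higher = more impaired (stated). Delta as written = O − S. Intended discrepancy = objective impairment minus reported impairment = −O − S, positive when tests are worse than complaints.

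**1. Four patient profiles, illustrative z = ±1.5, both sides at SD 1**

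| Profile | O | S | O − S (as written) | −O − S (tests inverted) |
|---|---|---|---|---|
| Impaired, unaware | −1.5 | −1.5 | 0 | +3.0 |
| Impaired, aware | −1.5 | +1.5 | −3.0 | 0 |
| Unimpaired, accurate | +1.5 | −1.5 | +3.0 | 0 |
| Unimpaired, over-complaining | +1.5 | +1.5 | 0 | −3.0 |

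As written, the accurate unimpaired patient is flagged and the unaware patient is not. Two other codings are possible. Inverting only S gives −3.0 for the unaware patient (wrong sign). Inverting both gives 0 (no signal). Only inverting the tests satisfies both the construct and the sign rule.

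**2. Fluency/DEX version (one z against one z)**

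Cov(O − S, −O − S) = −(Var O − Var S) = −(1 − 1) = 0, whatever the correlation between O and S. A simulation of 1,000,000 normal pairs, with that correlation assumed at 0, −0.3, −0.6 and −0.9, gave correlations of 0.00. P(delta > 0) was 0.50 with or without impaired awareness. The written delta instead tracked performance, with correlation 0.71 to 0.98.

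**3. General version (sum of k tests against one z)**

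Assumptions not in the document: each z has variance 1, the common inter-test correlation r is 0 to 0.5, and O and S are uncorrelated. Var(sum) = V = k + k(k − 1)r. Share of delta's variance due to the tests = V/(V + 1).

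| k | r | V | Share |
|---|---|---|---|
| 5 | 0 | 5 | 5/6 = 83% |
| 5 | 0.3 | 11 | 11/12 = 92% |
| 5 | 0.5 | 15 | 15/16 = 94% |
| 10 | 0 | 10 | 10/11 = 91% |
| 10 | 0.3 | 37 | 37/38 = 97% |
| 10 | 0.5 | 55 | 55/56 = 98% |

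The share is the same whether or not the tests are inverted. Without inversion, delta also runs against the construct. Its correlation with the intended discrepancy depends on how that discrepancy is scaled:

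- Raw sum kept in the discrepancy: −(V − 1)/(V + 1). At r = 0.3 this is −10/12 = −0.83 (5 tests) or −36/38 = −0.95 (10 tests).
- Sum rescaled to SD 1 in the discrepancy: −(√V − 1)/√(2(V + 1)). At r = 0.3 this is −2.32/4.90 = −0.47 or −5.08/8.72 = −0.58.

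Over r = 0 to 0.5 the two forms run from −0.67 (V = 5) to −0.96 (V = 55), and from −0.36 (V = 5) to −0.61 (V = 55).

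**4. Number of tests per visit**

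If all tests is taken literally, k is 10 at baseline and 5 afterwards. A patient stable at z = −1 on every test then moves from a sum of −10 to −5. Delta changes by 5 units with no change in performance or awareness.

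**The case against.** The strongest reply is that the article never gives a coding direction for the test z-scores. It does give the construct and the sign, and exactly one coding fits both: tests oriented so that higher means worse. An unreported recoding in a condensed article is a plausible explanation, and one sentence would cure it. This stands as a limit. A reader might infer that the trial's ISAc results are bound to be wrong, and the document does not support that. It supports only that the text, followed as printed, gives the wrong score. Recoding would leave the scale mismatch in the general version untouched.

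Four further inferences go too far:

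- **Correlation 0 and 50% for every ISAc score.** These hold only when both sides have SD 1, as in the fluency/DEX version. The summed version has a different variance and gives negative correlations. Conversely, the variance shares do not apply to the fluency/DEX version.
- **A biased treatment effect from dropping tests.** The ten-then-five reading is one interpretation, since the article ties the full battery to classifying mild cognitive impairment. Even so, Study Design states that all patients complete the same tests in the same order, and the analysis includes the group-by-time interaction. The shift falls on both arms alike, so what it distorts is the change scores themselves.
- **An error over timed tests.** Reversing timed measures is routine scoring detail that an article can leave to the full protocol.
- **A threat to the main result.** The primary ISAm score is built from rated motor discrepancies and does not use this formula.

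**Conclusion.** The point holds in this form: the ISAc formula and its sign rule contradict each other as written, and the general version puts the two sides on different scales.

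The sign contradiction rests on reading performance as higher = better with no inversion, which is the natural reading but an inferred one. On that reading the fluency/DEX delta carries no linear information about the intended discrepancy, and the general delta runs opposite to it. The scale mismatch does not depend on direction. Its size (83–94% for 5 tests, 91–98% for 10) rests on the assumed inter-test correlations of 0 to 0.5 and on uncorrelated objective and subjective scores. The change in the number of tests is conditional on the literal reading of all tests.

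Because ISAc is one of several secondary outcomes and the primary outcome is unaffected, this is a should-fix.

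**What to change.** Three changes to the scoring definition:

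1. State that every test z-score is oriented so that higher means more impaired before delta = objective minus subjective is formed. The existing sign rule then holds, in both the general and the fluency/DEX version.
2. Build the general objective composite from the same five Test I measures at all three visits, and say so.
3. Re-standardise that composite to the questionnaire's scale (SD 1), using baseline means and SDs held fixed for all visits, so that real change over time is kept.

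The cost is wording and scoring syntax. No assessment is added or dropped, and the Test II measures remain available at baseline for classifying mild cognitive impairment. If the recoding is already in the working syntax, the first change is one sentence.

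### The ISAc delta contradicts itself on direction: as printed, a positive score does not mark impaired self-awareness of cognition unless test scores are first turned so that higher means worse

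*Protocol article*

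**What the plan says.** Everything needed is in the Protocol article, Methods, under Impaired Self-Awareness of Cognition. That section fixes five things.

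- **Direction of the subjective score.** For the CFQ and the DEX: "Higher scores reflect higher subjective impairment in both questionnaires".
- **Standardisation.** The section states that "questionnaire and neuropsychological test raw data is transformed into standardized z-scores to allow better comparison". It mentions no change of sign.
- **Objective score.** For the general index, "the transformed values of all neuropsychological tests are either summed up for reflecting general cognitive performance". For the executive index, "only verbal fluency performance is taken into account to reflect executive cognitive performance".
- **Formula.** "A delta score is calculated by subtracting subjective scores from objective scores".
- **Meaning.** "Impaired self-awareness of cognition occurs if objective neuropsychological test performance appears to be worse than subjective impairment in everyday life". The next sentence adds: "This is reflected by a positive delta score".

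Outcome Measures lists ISAc among the secondary outcomes, both from baseline to post-measurement and from baseline to follow-up. Planned Statistical Analyses also uses cognitive self-awareness in the imaging work.

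**The concern.** The formula subtracts a score that rises with impairment from a score that, as described, rises with performance. Such a difference runs from poor performance with many complaints at the low end to good performance with few complaints at the high end. Both ends are patients whose self-report agrees with their test results. The patient of interest, who performs poorly and does not notice, falls in the middle.

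If the rule were followed as printed, the ISAc outcome, its change under IPSUM and its imaging correlates would rest on an index that does not separate aware from unaware patients. Change over time would also be misread. The Introduction considers better attention and executive functioning possible under mindfulness training, and any gain in fluency would push the printed delta upwards, towards impaired awareness.

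**Working it through.** **Inputs.** P is the objective z-score, higher = better, as the section's word for it implies and as holds for verbal fluency. S is the subjective z-score, higher = more complaints, as stated. The formula is objective minus subjective, and a positive value is said to mean ISAc. The article gives no correlation r between P and S, so r is left free.

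**Step 1: can the sign rule be reproduced?** Four patient profiles at |z| = 1, under each possible coding:

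| Profile (P, S) | As printed: P - S | Objective reversed: -P - S | Subjective reversed: P + S | Both reversed: -P + S |
|---|---|---|---|---|
| Poor performance, few complaints (-1, -1): the ISAc patient | 0 | **+2** | -2 | 0 |
| Good performance, few complaints (+1, -1) | **+2** | 0 | 0 | -2 |
| Poor performance, many complaints (-1, +1): aware | -2 | 0 | 0 | +2 |
| Good performance, many complaints (+1, +1) | 0 | -2 | +2 | 0 |

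The printed rule is not reproduced. Only reversing the objective score alone gives the ISAc patient a positive value, both concordant profiles 0, and the over-complainer a negative value. With a more extreme test score (P = ±1.5, S = ±1), the printed delta is -1.5 - (-1) = -0.5 for the ISAc patient and 1.5 - (-1) = +2.5 for the good performer with few complaints.

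**Step 2: how much of the intended quantity does the executive delta carry?** Let D = P - S (printed) and I = -P - S (intended), with Var(P) = Var(S) = 1 and Cov(P, S) = r.

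Cov(D, I) = -Var(P) - r + r + Var(S) = -1 + 1 = 0.

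The correlation is zero for every r. In a simulation of 400,000 bivariate normal patients at r = 0, -0.2 and -0.4, the correlation was 0.00 to two decimals each time. Among patients with below-average performance and below-average complaints, about 50% had a positive printed delta. Among those with above-average performance and below-average complaints, 100% did. After reversal of the objective score, 100% of the first group were positive.

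**Step 3: change over time.** If fluency rises by a and complaints fall by a, D changes by a - (-a) = +2a, while I changes by -a - (-a) = 0. The printed rule would report worse awareness where the discrepancy has not moved.

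**Step 4: scale of the general score.** After baseline, one test per domain is repeated, so five z-scores are summed. With a common inter-test correlation ρ, which the article does not give and is assumed here, the SD of the sum is √(5 + 20ρ):

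- ρ = 0: √5 = 2.24
- ρ = 0.3: √11 = 3.32
- ρ = 0.5: √15 = 3.87

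The CFQ z-score has SD 1. Unless the sum is rescaled, the general delta is mostly test score, whichever way that score is oriented.

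**The case against.** The strongest reply is that the intended direction can be recovered from the section itself. It says in words what ISAc is and ties that to a positive sign, and Step 1 shows that only one coding fits. The authors may well reverse the test scores in practice, and the sign of each test is scoring detail that an article may leave to a fuller document. This stands as far as intent goes: a reader might infer that the analysis will be run on an uninformative index, and the document does not show that. It does not remove the contradiction. The article chose to print the formula, the preparatory step and the sign rule, and those, with the quantity described as performance, disagree.

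Two further inferences go too far.

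- **That the general score is reversed, not merely uninformative.** A negative correlation with the intended index does appear if the five-test sum is left unscaled. It comes from the sum's larger variance under an assumed ρ (11 against 1 at ρ = 0.3). Once the sum is re-standardised, Step 2 applies and the correlation is 0.
- **That the sum demonstrably mixes directions because Trail Making is timed.** Trail Making is in the Test II column of Table 1, and only Test I measures are repeated after baseline. The article does not name the scored variables, so timed scoring is an assumption.

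It is also fair to say that the Discussion already describes the ISAc analyses as not validated. That is a caveat about the method and does not cover a conflict of sign.

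**Conclusion.** The point holds as an internal contradiction in the scoring of a secondary outcome. On the literal reading, the executive delta has zero correlation with the discrepancy it is meant to measure, and it labels good performers with few complaints as impaired. This rests on two things: the objective z-score is higher = better, as described, and both scores have unit variance. No assumption about the correlation between performance and complaints is needed. For the general score, the same orientation conflict applies and the scales are unequal as well; the size of that inequality depends on inter-test correlations that the article does not give.

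Severity is moderate. The primary ISAm score is calculated separately from video ratings and is untouched, as are the sample size and the interim analyses. The collected data do not depend on the sign, so the score can still be computed correctly at analysis.

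**What to change.** In the section on Impaired Self-Awareness of Cognition:

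1. State that every objective test z-score is oriented so that higher = worse before it is used or combined, naming the scored variable and its direction for each test.
2. Keep the formula, reworded as objective impairment z minus subjective impairment z, with positive = ISAc. The existing sign rule is then correct.
3. For the general score, re-standardise the summed z-scores (or average and then re-standardise them) so that they are on the same scale as the CFQ z-score before subtraction.

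If the scores are already reversed in practice, item 1 only records what is done. The cost is a few sentences, with no new data and no change to the visits.
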